**INVESTIGATORS**

Principal Investigator: [name] MD PhD MSc DTM&H

Clinical epidemiologist, Department of Medical Parasitology and Infection Biology

Swiss Tropical Institute

[name]

Postfach

[name]

Telephone number: [name]

Fax number: [name]

Email : [contact]

Co-principal investigator : [name] MD

Papua New Guinea Institute of Medical Research

[name]

Maprik Papua New Guinea

Telephone number: [name]

Fax number: [name]

Email : [contact]

PROTOCOL TITLE Efficacy and tolerance of COTRIFAZID (rifampicin, co- trimoxazole, isoniazid) against resistant malaria in semi-immune subjects: a multicentric, open, block- randomised, comparative trial

PROJECT PHASE III

SPONSOR Fatol Arzneimittel GmbH

INDICATION UNDER STUDY Resistant malaria

OBJECTIVES 1) To compare the efficacy of Cotrifazid versus Lariam (mefloquine) or standard treatment in semi-immune subjects with resistant malaria

2) To compare the tolerance of Cotrifazid versus Lariam or standard treatment in semi-immune subjects with resistant malaria

EXPERIMENTAL DESIGN

OF THE TRIAL Open, block-randomised, comparative

PLANNED SAMPLE SIZE 330 (110 Cotrifazid, 110 Lariam, 110  standard

treatment)

NUMBER OF CENTRES 2

SUBJECT SELECTION CRITERIA Subjects with resistant malaria (any species) with a weight > 5kg

SUBJECT EXCLUSION CRITERIA Pregnant women, infants less than 6 months of age, severe malaria

TREATMENT Cotrifazid (rifampicin, co-trimoxazole, isoniazid)

DOSAGE Subjects > 40 kg : 2 x 2 tablets per day for 7 days

Subjects < 40 kg and > 20kg : 2 x 1 tablet per day for 7d

Subjects < 20 kg : 2 x ½ tablet  per day for 7 d

SCHEDULE Every 12 hours

ROUTE OF ADMINISTRATION Oral

COMPARATOR I Lariam (mefloquine)

DOSAGE Subjects > 60 kg : 6 tabs (3, 2, 1)

Subjects > 40 kg and < 60 kg : 5 tabs (2, 2, 1)

Subjects < 40 kg and > 30 kg : 3 ½ tabs (1 ½ , 1, 1)

Subjects < 30 and > 20 kg : 3 tabs (1, 1, 1)

Subjects < 20 kg and > 10 kg : 1 ½ tabs ( ½ , ½, ½ )

Subjects < 10 kg : ¾ tablet ( ¼ , ¼, ¼ )

SCHEDULE Hour 0, 8, 24

ROUTE OF ADMINISTRATION Oral

COMPARATOR II Standard treatment (presently quinine + Fansidar)

DOSAGE Quinine

Subjects > 60 kg : 3 x 600 mg /day for 5 days Subjects < 60 kg : 3 x 10 mg/kg/day for 5 days

+

Fansidar as a single dose

Subjects > 40 kg : 3 tablets

Subjects < 40 kg and > 30 kg : 2 tablets

Subjects < 30 and > 20 kg 1 ½ tablet

Subjects < 20 kg and > 10 kg 1 tablet

Subjects < 10 kg ½ tablet

SCHEDULE Every 8 hours for quinine, hour 0 for Fansidar

ROUTE OF ADMINISTRATION Oral for quinine and Fansidar, or I.M. for quinine

Parameters OF EFFICACY 1. Fever clearance time

1. Parasite clearance time
2. Rate of early and late treatment failure (ETF, LTF)
3. Occurrence of complications

PARAMETERS OF TOLERANCE: 1. Reported Adverse Events (AEs)

2. Clinical and laboratory values

Secondary Parameters of EfficaCY 1. Symptom clearance time

2. Haemoglobin concentration

PROCEDURES

All subjects who are diagnosed with malaria (history of fever and no other major symptom, OptiMAL test positive) and have been already treated for malaria in the last 28 days can be included if they give their informed consent and if the clinician in charge would have given the standard treatment for resistant malaria in the absence of the study. A patient should not be included if the clinician prefers to use quinine for whatever reason, if the patient has one of the symptoms or signs of complicated or severe malaria(i.e. history of recent convulsion, any neurological sign or impairment of consciousness, temperature >40 C0, heavy vomiting, haemoglobinuria, respiratory distress, bleeding, circulatory collapse, shock, jaundice, haemoglobin < 5 g/dl), is less than 6 months of age or is pregnant. The patients will be randomised on the spot to have either Cotrifazid, Lariam or standard treatment (at present quinine + Fansidar). The treatment dosage and schedule for Cotrifazid will be the following : subjects > 40 kg : 2 x 2 tablets, subjects < 40 kg and > 20kg : 2 x 1 tablet, subjects < 20 kg : 2 x ½ tablet, ever 12 hours for 7 days. The treatment dosage and schedule for Lariam will be the following : subjects > 60 kg : 6 tabs (3 at hour 0, 2 at hour 8, 1 at hour 24), subjects > 40 kg and < 60 kg : 5 tabs (2, 2, 1), subjects < 40 kg and > 30 kg : 3 ½ tabs (1 ½ , 1, 1), subjects < 30 and > 20 kg : 3 tabs (1, 1, 1), subjects < 20 kg and > 10 kg : 1 ½ tabs ( ½ , ½, ½ ), subjects < 10 kg : ¾ tablet ( ¼ , ¼, ¼ ). Follow-up assessments will be done at hours 24, 48 and 72 (clinical, parasitological, pharmacological) and days 7 (clinical, parasitological, biochemical and pharmacological) and 14 (clinical, parasitological, haematological, pharmacological), or more intensively in case of persisting symptoms or pathological signs. Treatment will be changed to the standard treatment (at present quinine + Fansidar) if necessary (problems of tolerance, aggravation of clinical status, increase in parasitaemia etc with Cotrifazid or Lariam).

STATISTICAL ANALYSIS

EFFICACY :

1. Comparison of the fever clearance time in the Cotrifazid and comparator groups
2. Comparison of the parasite clearance time in the Cotrifazid and comparator groups
3. Comparison of the rate of ETF and LTF in the Cotrifazid and comparator groups
4. Comparison of the rate of complications in the Cotrifazid and comparator groups

5. Comparison of the haematological concentration in the Cotrifazid and comparator groups

TOLERANCE:

1. Comparison of the rate of adverse events in the Cotrifazid and comparator groups
2. Comparison of the type of adverse events in the Cotrifazid and comparator groups
3. Comparison of the rate of patients requiring an additional drug because of tolerance problems in the Cotrifazid and comparator groups (e.g. antivomiting)
4. Comparison of the biochemical and haematological results in the Cotrifazid and comparator groups

**1 JUSTIFICATION AND OBJECTIVES**

**1.1 Background and Rationale**

Malaria remains a serious health problem in most developing countries, with approx. 2.5 million deaths per year. One of the contributor to mortality is the spreading of malaria resistance first in Southeast Asia and then in Africa and the South Pacific. In Papua New Guinea (PNG), chloroquine-resistant falciparum malaria was first documented in 1976 (Yung and Bennett, 1976; Grimmond *et al.*, 1976). Since then, studies done in different provinces at different times showed the problem to be widespread and to increase gradually with a recent shift from RI to RII and RIII types (Dulay *et al.*, 1987; Schuurkamp, 1992; Trenholme *et al.*, 1993; Al-Yaman *et al.*, 1996). In the Wosera, [name] *et al*. (unpublished data,1998) showed that 16 to 26% of the patients who were treated with the standard regimen for uncomplicated malaria (amodiaquine or chloroquine) had a recrudescence of symptoms with parasitaemia.

Sulfadoxine/pyrimethamine (Fansidar)-resistant falciparum malaria was described in 1980 (Darlow *et al.*, 1980; Darlow *et al.*, 1982). As far as quinine is concerned, the first documented cases of in vivo resistance of *P. falciparum* in PNG were described in 1993 (Al-Yaman *et al.*, 1993), with a clear increase since then, in spite of a prolonged duration of treatment (5 days instead if 3).

Because of the above failures, the PNG medical authorities have planned to introduce gradually a new artemisinine derivative to replace quinine and Fansidar, which is the present standard regimen for complicated or resistant malaria. At present, the main problem is not the lack of potent drugs, but the lack of potent and cheap drugs. Indeed, the combination of atovaquone and proguanil (Malarone), or more recently the combination of benflumetol and artemether (Riamet) have proved to be safe and efficacious, but they are unaffordable for people living in endemic areas. Mefloquine (Lariam) has proved to be quite efficacious for a while in South East Asia against multiresistant falciparum malaria, and also reasonably cheap. In the last decade, treatment failures have become more frequent and artemeter was added in combination with mefloquine to the standard treatment regimen for falciparum malaria in multidrug resistant areas of Thailand (Price et al, 1995). It is possible that a fixed combination (artemisinine derivative + mefloquine) will be available in the future to fight multiresistant parasites in highly endemic areas. In this context, testing mefloquine alone in PNG is a step towards the development of safe and efficacious drugs and drug combinations for the country when quinine and Fansidar will not be sufficient anymore.

In the same sense, the development of Cotrifazid is promising. Indeed it meets most of the requirements for a new drug for resistant malaria, which are the following : it is a combination made of relatively short-acting compounds (decreasing the rapid spread of resistant strains) ; it is active against resistant strains of *Plasmodium falciparum* in vitro and it is efficacious in mice infected with resistant strains (Brun *et al*., unpublished data) ; it is likely to be safe since the compounds have been used either alone or in combination for a very long time for the treatment of tuberculosis for example, with higher dosage for a much longer duration ; it is likely to be cheap (approx. 5 dollars for a full treatment).

There have been some studies conducted with Cotrifazid in humans living in endemic areas, including infants of less than 6 months of age (Freerksen *et al.*, 1995,1996, Goerg *et al.*, in press). All these studies showed Cotrifazid to be safe and efficacious for the treatment of falciparum malaria, whether uncomplicated, complicated or resistant (Goerg *et al*, in press). It is required to have additional hard data in terms of efficacy against resistant malaria, and also to know about efficacy in geographical areas other than Africa.

The rationale to use this combination is based on animal and human experiments. Rifampicin is active against *Plasmodium berghei* malaria in rodents (Alger et al, 1970 ; Brun, unpublished data). Numerous studies showed co-trimoxazole to be efficacious in the treatment of malaria in humans (Bloland et al, 1991 ; Hansford et al, 1982 ; Hutchinson & Farquhar, 1982). There is a pharmacokinetic synergism between co-trimoxazole and rifampicin, with increase of t50 and AUC when administered simultaneously (Bhatia et al, 1991). Isoniazid has no clear anti-plasmodial activity. It has only been shown to delay malaria mortality in mice, and to reduce overall parasite load when given in combination with rifampicin and co-trimoxazole (Brun, unpublished data). This may be due to an effect of isoniazid on blood cytokines, in particular TNF-alpha, since isoniazid did protect mice against endotoxin lethality (Urbaschek et al, 1991). The last argument to include isoniazid in the combination is to avoid the selection of resistant mycobacteria when treating for malaria an undiagnosed tuberculous patient. This risk has been revisited recently, and clear-cut evidence was presented that such a event was extremely improbable (Mueller-Brundaler et al, 1997). Even WHO, when defining a case of ‘previously untreated’ pulmonary tuberculosis for the purpose of an eventual ‘primary drug resistance’ identification, accepts for such a patient a previous antituberculous chemotherapy of up to 1 month duration (WHO, 1997). This is based also on the experience that, even with rifampicin monotherapy, the probability of selecting for rifampicin resistance of tubercle bacilli is very low. Moreover, should one fear the possibility of a not recognized advanced pulmonary tuberculosis case receiving Cotrifazid for malaria, then isoniazid as the usual combination drug for treatment of that disease would offer an additional protection against the selection of rifampicin-resistant bacilli.

Study area

Within the Malaria Vaccine Epidemiology and Evaluation Project (MVEEP) situated in the Wosera in Maprik District, East Sepik Province, and in Yagaum, Madang Province (Alpers *et al.*, 1992), we have conducted baseline studies of the epidemiology and transmission of malaria, specific parasitological and immunological studies, as well as clinical and drug resistance studies (see Cattani et al 1986, Cox et al 1994, [name] *et al.*, 1994a,b, 1995, 1997). Infrastructure including research offices and laboratories, as well as accommodation are in place. These facilities are all within 5 minutes walk of the outpatient clinics and hospitals where the study will take place.

**1.2 Objectives of the Trial**

The purpose of this trial is to assess the efficacy and safety (primary parameters) of Cotrifazid in semi-immune Papua New Guinean patients with resistant malaria.

More specifically i) to compare the efficacy of Cotrifazid versus Lariam (mefloquine) or standard treatment in semi-immune subjects with resistant malaria, and ii) to compare the tolerance of Cotrifazid versus Lariam or standard treatment in semi-immune subjects with resistant malaria.

**2 GENERAL DESIGN**

**2.1 Overall Design**

This is an open, block-randomised, comparative, multicentric study.

All subjects presenting at the outpatient clinic or admitted in the ward of the Maprik Hospital and Yagaum Health Center who are diagnosed with malaria (history of fever and no other major symptom, OptiMAL test positive) and have been already treated for malaria in the last 28 days can be included if they give their informed consent and if the clinician in charge would have given the standard treatment for resistant malaria in the absence of the study. A patient should not be included if the clinician prefers to use quinine for whatever reason, if the patient has one of the symptoms or signs of complicated or severe malaria (i.e. history of recent convulsion, any neurological sign or impairment of consciousness, temperature >40 C0, heavy vomiting, haemoglobinuria, respiratory distress, bleeding, circulatory collapse, shock, jaundice, haemoglobin < 5 g/dl), has contra-indications for mefloquine (history of psychiatric disorder, epilepsy), is less than 6 months of age, or is pregnant. The patients will be randomised on the spot to have either Cotrifazid, Lariam or standard treatment (at present quinine + Fansidar). The treatment dosage and schedule for Cotrifazid will be the following : subjects > 40 kg : 2 x 2 tablets, subjects < 40 kg and > 20kg : 2 x 1 tablet, subjects < 20 kg : 2 x ½ tablet, ever 12 hours for 7 days. The treatment dosage and schedule for Lariam will be the following : subjects > 60 kg : 6 tabs (3 at hour 0, 2 at hour 8, 1 at hour 24), subjects > 40 kg and < 60 kg : 5 tabs (2, 2, 1), subjects < 40 kg and > 30 kg : 3 ½ tabs (1 ½ , 1, 1), subjects < 30 and > 20 kg : 3 tabs (1, 1, 1), subjects < 20 kg and > 10 kg : 1 ½ tabs ( ½ , ½, ½ ), subjects < 10 kg : ¾ tablet ( ¼ , ¼, ¼ ). Follow-up assessments will be done at hours 24, 48 and 72 (clinical, parasitological and pharmacological), and days 7 (clinical, parasitological, biochemical, and pharmacological) and 14 (clinical, parasitological, haematological, and pharmacological), or more intensively in case of persisting symptoms or pathological signs. Treatment will be changed to the standard treatment (at present quinine + Fansidar) if necessary (problems of tolerance, aggravation of clinical status, increase in parasitaemia etc).

All blood samples will be taken by venepuncture (2 ml).

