**3.3 Exclusion Criteria**

A subject is not eligible if one or more of the following parameters are fulfilled:

- History of allergy to drug compounds
- Unable to swallow
- Signs of severe malaria (i.e. history of recent convulsion, any neurological sign or impairment of consciousness, temperature >40 C0, heavy vomiting, , haemoglobinuria, respiratory distress, bleeding, circulatory collapse, shock, jaundice, haemoglobin < 5 g/dl)
- Contra-indications for Lariam (history of psychiatric disorder, epilepsy)
- Less than 6 months of age
- Pregnancy

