**4.1 Names and Formulations**

Cotrifazid is a combination made of rifampicin 112.5 mg, sulphamethoxazole 200 mg + trimethoprim 40 mg, and isoniazid 75 mg.

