**5** **STUDY PROCEDURES**

**5.1 Drug**

**5.1.1 Drug Administration**

**5.1.1.1 Dosage Regimen & Rationale for Selection**

The treatment dosage and schedule for Cotrifazid will be the following : subjects > 40 kg 2 x 2 tablets, subjects < 40 kg and > 20kg  2 x 1 tablet, subjects < 20 kg  2 x ½ tablet, every 12 hours.

The treatment dosage and schedule for Lariam will be the following : subjects > 60 kg : 6 tabs (3 at hour 0, 2 at hour 8, 1 at hour 24), subjects > 40 kg and < 60 kg : 5 tabs (2, 2, 1), subjects < 40 kg and > 30 kg : 3 ½ tabs (1 ½ , 1, 1), subjects < 30 and > 20 kg : 3 tabs (1, 1, 1), subjects < 20 kg and > 10 kg : 1 ½ tabs ( ½ , ½, ½ ), subjects < 10 kg : ¾ tablet ( ¼ , ¼, ¼ ).

The treatment dosage and schedule for quinine will be the following : subjects > 60 kg  3 x 600 mg quinine /day, subjects < 60 kg  3 x 10 mg/kg/day every 8 hours.

The treatment dosage and schedule for Fansidar will be the following : subjects > 40 kg  3 tablets, subjects < 40 kg and > 30 kg 2 tablets, subjects < 30 and > 20 kg 1 ½ tablet, subjects < 20 kg and > 10 kg 1 tablet, subjects < 10 kg ½ tablet.

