**5.1.1.3 Duration**

Cotrifazid will be given for 7 days.

Lariam will be given for 24 hours.

Quinine will be given for 5 days.

Fansidar will be given as a single dose at day 0.

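### The default, and only named, switch treatment for tolerance problems on Cotrifazid contains a second sulphonamide, with no exception for a suspected sulphonamide or hypersensitivity reaction

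*Protocol*

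**What the plan says.** The switch rule stands in two places. Section 2.1 reads: "Treatment will be changed to the standard treatment (at present quinine + Fansidar) if necessary (problems of tolerance". The Procedures part of the synopsis gives the same rule and names the arms and reasons: "problems of tolerance, aggravation of clinical status, increase in parasitaemia etc with Cotrifazid or Lariam". Tolerance is the first reason listed, and quinine + Fansidar is the only regimen named.

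The drugs are identified elsewhere in the protocol:

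- Section 4.1 lists, among the components of each Cotrifazid tablet, "sulphamethoxazole 200 mg + trimethoprim 40 mg".
- Section 1.1 gives the composition of Fansidar in passing: "Sulfadoxine/pyrimethamine (Fansidar)-resistant falciparum malaria was described in 1980".
- Section 5.1.1.3 states how it is given: "Fansidar will be given as a single dose at day 0".

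One safeguard bears on allergy. Section 3.3 excludes patients with "History of allergy to drug compounds".

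**The concern.** Tolerance problems are of many kinds. For most of them, vomiting for example, a change to quinine + Fansidar raises no question of drug class. The exception is a rash or other reaction that suggests hypersensitivity to the sulphonamide in Cotrifazid. For that patient the written default supplies another sulphonamide.

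Two features make this worth correcting. Cotrifazid is a fixed combination, so a clinician who sees such a reaction cannot readily tell which component caused it and cannot rule out the sulphonamide when choosing the rescue. And Fansidar is one dose, so once given it cannot be stopped partway, whereas Cotrifazid is a seven-day course. What is at stake is patient safety, not the analysis.

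**Working it through.** No arithmetic applies. The check sets the relevant provisions side by side and asks of each whether it removes Fansidar from the rescue of a Cotrifazid patient with a suspected sulphonamide reaction.

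1. **Which patients.** The synopsis applies the rule to Cotrifazid and Lariam. Lariam is mefloquine, which is not a sulphonamide, so Lariam patients who switch are not re-exposed. Patients on standard treatment are already receiving it. The issue is confined to the Cotrifazid arm.

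2. **Which drugs.** Sulphamethoxazole is in Cotrifazid (section 4.1) and sulfadoxine is in Fansidar (section 1.1). The protocol names both drugs but not their class. That both are sulphonamides is general pharmacology and is the one outside fact used here.

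3. **The switch rule (synopsis, section 2.1).** The qualifier about necessity governs whether to switch, not to what. The words indicating that the standard regimen is the present one allow it to change later, but do not vary it by patient. Fansidar is not removed.

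4. **Allergy exclusion (section 3.3).** This acts at entry and on history. It cannot reach a reaction that first appears on treatment.

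5. **Withdrawal (section 6.1).** Adverse events are a separate ground for withdrawal and no drug is prescribed under that ground. The investigator may withdraw a patient in the patient's own interest, and a patient who withdraws keeps the right to treatment. This permits leaving Fansidar out, but names nothing to give instead. The ground for complications again sends Cotrifazid patients to standard treatment. Its reference to other drugs follows the clause on patients already taking quinine + Fansidar and concerns complications, not tolerance.

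6. **Concomitant medication (section 5.1.3).** Amodiaquine, chloroquine and tetracyclines are barred. Whether the bar continues after a switch is not stated. If it does, the alternatives narrow further.

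7. **Adverse event follow-up (section 5.2.4).** Events must be documented and followed until resolved or explained. The rescue regimen is not altered.

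The result is a default that includes Fansidar, discretion that allows departure from it, and no provision that names a sulphonamide-free rescue.

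For the remedy, section 5.1.1.1 already gives weight-based doses of quinine and of Lariam, so no new drug or dose table is needed. Contra-indications to Lariam are screened under section 3.3, but, like the allergy criterion, only at entry.

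**The case against.** The strongest reply is that a reader might infer from the switch rule that the protocol compels a second sulphonamide, and that it does not. The rule is a one-sentence general default with an open-ended list of reasons. Section 6.1 deals with adverse events separately and leaves the treatment open. The trial is open-label (section 4.2), dosing is supervised for the first three days (section 5.1.1.4), and patients are seen daily for the first four (section 5.2.1). The clinician therefore knows what the patient is taking. Withholding a drug related to one that has just caused a reaction is ordinary prescribing, and the allergy exclusion shows that the protocol already regards allergy as a bar to these drugs. The protocol also says nothing about cross-reactivity and gives no reaction rate.

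Most of this stands. It rules out any claim that patients are bound to receive Fansidar, and it means that no rate of harm can be stated. It does not remove the point. The default is written down, tolerance heads its reasons, and the protocol offers nothing to use in its place. A clinician who follows the text gives Fansidar, and one who does not must improvise.

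It may also be said that the remedy returns the choice to the clinician's discretion. It does so in part, but with the one regimen in question removed and two dosed alternatives named.

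**Conclusion.** The point holds as a limited patient-safety improvement. The default switch treatment should carry an exception for a suspected sulphonamide or hypersensitivity reaction on Cotrifazid, and it carries none.

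Its size cannot be derived. The protocol gives no rate of such reactions, of switches for them, or of cross-reaction between the two drugs. That the number is small is a judgement, because only Cotrifazid patients switched for this kind of reaction are concerned. A reader might take the whole Cotrifazid arm as the number at risk, or add a full seven-day sulphamethoxazole dose to the Fansidar dose. Neither measures risk: the arm size says nothing about how many react, and a patient switched for a reaction would usually stop before completing the course. Nor does the point extend to Lariam patients or to other tolerance problems.

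The conclusion rests on the two drugs belonging to one class, and on Fansidar being given at a switch as it is in the standard arm, as one dose. No estimate, test or sample size is affected.

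**What to change.** Add one sentence after the switch rule in the synopsis and in section 2.1: *A Cotrifazid patient with a suspected sulphonamide or hypersensitivity reaction receives rescue without Fansidar (quinine alone or, after re-checking contra-indications, Lariam).* The re-check matters because the Lariam criteria are otherwise applied only at entry.

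The cost is small: the same sentence in two places, and drugs already dosed in the protocol. There are two drawbacks. A few patients leave the uniform rescue path. And quinine alone is not an ideal substitute in patients enrolled for resistant malaria, since section 1.1 reports quinine resistance in the country "with a clear increase since then, in spite of a prolonged duration of treatment". The clinician must weigh that against Lariam for the individual patient.
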